#### Clinical oral health assessment

Oral hygiene status will be assessed by Silness and Löe Plaque Index (PI) [23]. The PI will be assessed at six sites per tooth and charted on all permanent teeth. The criteria for the Silness and Löe PI are as follows: 0 = no plaque detected with probe, 1 = plaque not visible by unaided eye but detectable with probe, 2 = moderate amount of plaque, and 3 = abundance of plaque. The percentage of tooth sites with moderate to abundant plaque (PI score, 2 or 3) will be calculated for each subject. Gingival bleeding will be assessed by the Gingival Bleeding Index (GBI) [24]. The GBI will be charted on all permanent teeth and assessed at six sites per tooth. The criteria for GBI are 0 = no bleeding after probing and 1 = presence of bleeding within 10 s after probing. The percentage of bleeding sites (GBI score, 1) will be calculated for each subject. At each study visit, ~ 10% of the subjects will be randomly selected for the reevaluation of the PI and GBI and the intra-rater reliabilities will be evaluated. Other clinical oral health outcomes including dental caries experience (DMFT), oral mucosa conditions, and dental prosthesis status will be recorded according to WHO Basic Oral Health Survey Guidelines [25].

#### Subjective health assessments

The subjective health assessment includes generic health-related quality of life (HRQoL) and oral health-related quality of life (OHRQoL) assessments. Patients will be interviewed with Chinese versions of the Short Form Health Survey 12 (SF-12) [26], the Oral Health Impact Profile 14 (OHIP-14) [27], and the Geriatric Oral Health Assessment Index (GOHAI) [28]. The SF-12 consists of 12 items, and each of them has its own physical component summary (PCS) and mental component summary (MCS) regression coefficients [29]. The response to each item will be multiplied by its PCS regression coefficient and added together with the PCS constant to provide Physical Health summary scores (SF-12 PCS). Mental Health summary scores (SF-12 MCS) will be calculated likewise. For OHIP, responses to the frequency of an event occurring as described by each item are coded on a 5-point Likert scale: 0 = never, 1 = hardly ever, 2 = occasionally, 3 = fairly often, and 4 = very often/all of the time. Summary OHIP-14 score and domain scores will be derived by summating responses to each item (i.e., scores 2, 3, and 4) [30]. For GOHAI, responses to the frequency of an event occurring as described by each item are coded using a 5-point Likert scale: 1 = always, 2 = often, 3 = sometimes, 4 = seldom, and 5 = never. Summary GOHAI scores will be derived by summating responses to items after reversing the coding of the three positively worded items (swallowing, appearance, and discomfort when eating) [31].

#### Collection of other confounding factors

Information will be also recorded regarding sociodemographic profiles (age, gender, education level, working status, and social pension), history of smoking, tooth brushing habit, time since last dental visit, dominant hand function as assessed by grip strength, cognitive ability as assessed by Mini-Mental State Examination [32], and number of comorbidities.

#### Data management

The principal investigator will oversee the data collection, entry, analyses, and reporting. Two researchers in our team will conduct data proofreading after the completion of data entry. The data will be securely stored in SPSS files in a computer with a password. The statistics software packages SPSS 25 for Windows (SPSS Inc., Chicago, USA) and QIIME 2 will be used to analyze the data. Per-protocol (PP) will be employed for both primary and secondary outcomes in bivariate analyses. Within- and between-group comparisons will be conducted over the clinical trial period. When the outcome variables are continuous and follow a normal distribution, a paired *t* test for related samples will be performed to determine the significant differences over time within a group. The Student *t* test for independent samples will be performed to compare the mean of the outcomes between the groups at baseline and follow-up reviews. When the outcome variables are continuous but do not follow a normal distribution, the Wilcoxon signed-rank test will be performed to determine the significant differences over time within a group. The Mann-Whitney *U* test will be employed to compare the differences in the rank of outcomes between the groups at baseline and follow-up reviews. When the outcome variables are categorical, the McNemar test will be performed to identify the changes in prevalence over time within a group. The chi-square test will be employed to compare the variations in prevalence between the groups at baseline and follow-up reviews. Regression analyses will be employed to address the effect of confounding factors for outcomes. When conducting the regression analysis, the method of Last Observation Carried Forward (LOCF) will be employed to deal with missing outcomes at follow-up reviews. Linear regression will be adopted when the dependent variables are continuous, and the residuals of the regression followed a normal distribution. Negative binomial regression will be adopted when the distribution of the continuous dependent variables is over-dispersed. Logistic regression will be adopted when the dependent variables are binary.

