The following selection criteria are applied: (1) having onset of stroke within 3 days and free of any post-stroke complication; (2) having moderate to severe functional disability—Barthel Index (BI) scores of < 70; (3) being conscious and respiring voluntarily without ventilator; (4) not having any lung disease and lower respiratory infection; (5) not having indwelling naso-gastric feeding tubes; (6) having dysphagia as shown by Gugging Swallowing Screen (GUSS) test; (7) having normal cognitive ability or mild impairment—Mini-Mental State Examination (MMSE) > 18; (7) having the ability to follow instructions (as an assessment of compliance of oral health intervention); (8) not having systemic administration of antibiotics; and (9) not being edentulous. Patients who meet the above selection criteria will be provided with detailed information regarding potential benefits and adverse effects of the interventions, the procedures of this trial, and the anticipated outcomes. They will be asked by a researcher in our team to sign on a written informed consent before enrolling in this study (written informed consent, additional file 3).

According previous studies [12, 13], pneumonia complicating stroke usually occurs within 1 week after stroke. We set the prevalence of pneumonia within 1 week after onset of stroke as the primary outcome of this study since we would like to explore whether oral health promotion interventions could possibly reduce the prevalence of pneumonia after stroke. According to previous epidemiological studies, the prevalence of pneumonia complicating stroke is 20 to 60% [12, 13]. Thus, we hypothesize that in the comparison group, the prevalence of pneumonia complicating stroke within 1 week is 40%, while the prevalence could be decreased to the lower limit of 20% in the interventional group. We set the statistical power at 80% and the statistical significance level at 0.05. Anticipating a 10% dropout rate over the first week of this clinical trial, the initial sample size for each group is proposed as 83 patients per group (166 subjects in total, Gpower 3.0.10 statistical software).

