Immediately after group assignment, the subjects and their primary caregivers in the interventional group will be invited to a one-to-one workshop provided by a dental professional regarding oral hygiene. This content of this workshop includes the importance of oral health following stroke and how to implement standardized oral hygiene care (Bass brushing technique, flossing, mouthwash use, and cleaning partial dentures). The primary caregivers will be responsible for carrying out the oral hygiene care for the patients with stroke. After the demonstration, the primary caregivers will be asked to perform their oral hygiene care skills and will be corrected by the dental professional if oral health care is not conducted appropriately. For those in the interventional group, they will be provided with a powered toothbrush and its manufacturer instructions. In addition, they will be given 0.2% chlorhexidine gluconate mouthwash. They will be asked to use a powered toothbrush to brush their teeth and rinse twice daily with 10 ml of the mouth rinse (at least 30 min after brushing). For those subjects in the comparison group, they will be only provided with oral hygiene instruction in the one-to-one workshop. Due to ethical considerations, those subjects in the comparison group will be given the same oral hygiene products after the completion of the clinical trial. Participants may withdraw from this study at any time points. Participants who will have systemic antibiotic use longer than 1 week after interventions will be excluded from this study.

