### Outcomes

The primary outcome is the prevalence of pneumonia complicating stroke within 1 week after baseline. The secondary outcomes include the following: (1) the prevalence of pneumonia complicating stroke within 1, 3, and 6 months after baseline; (2) metagenomic outcomes in terms of composition and relative abundance of oral microbiome in oral rinse samples in 3, 5, and 7 days, and 1, 3, and 6 months after baseline; (3) oral hygiene status and gingival bleeding in 1, 3, and 6 months after baseline; and (4) generic health-/oral health-related quality of life in 1, 3, and 6 months after baseline. The time point for assessing each outcome is illustrated in Fig. 1.

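### The primary pneumonia comparison is fixed in the per-protocol set although the hypothesis is superiority and no all-randomised analysis is named; the bias can run either way

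*Protocol article*

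**What the plan says.** - **Outcome.** The Outcomes section states: "The primary outcome is the prevalence of pneumonia complicating stroke within 1 week after baseline".
- **Hypothesis.** The sample-size paragraph under Participants assumes 40% pneumonia within a week in the comparison group, and says that "the prevalence could be decreased to the lower limit of 20% in the interventional group". The stated aim is to reduce pneumonia. The Background nevertheless calls the trial an equivalence trial. It gives no margin, and neither the hypothesis nor the sample size is one of equivalence.
- **Analysis set.** Data management says: "Per-protocol (PP) will be employed for both primary and secondary outcomes in bivariate analyses". No other analysis set is named.
- **Test.** The same section says: "The chi-square test will be employed to compare the variations in prevalence between the groups at baseline and follow-up reviews". This is the bivariate comparison of pneumonia between groups.
- **Second analysis.** Regression is planned to address confounding, logistic for binary outcomes, and for it "the method of Last Observation Carried Forward (LOCF) will be employed to deal with missing outcomes at follow-up reviews". Its analysis set is not stated, and it is not declared primary.
- **Ways out of the set.** Interventions says: "Participants may withdraw from this study at any time points". It also excludes participants whose systemic antibiotic use exceeds one week after the interventions. Both rules apply to both arms. Subjects know their allocation.
- **Expected loss.** 10% dropout is anticipated in the first week, with 83 patients recruited per group.

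**The concern.** A superiority trial draws its validity from comparing the groups as randomised. A per-protocol set is chosen by events after randomisation, and here several of those events could be related to pneumonia:

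- The regimens are unequal. One arm must use a powered brush and rinse twice daily; the other receives instruction only. Failure to follow the protocol is therefore easier in one arm than in the other.
- Patients who do badly in the first week may be both harder to treat as assigned and more likely to develop pneumonia.
- A long course of systemic antibiotics is plausibly a consequence of pneumonia, so that exclusion can remove the outcome events themselves.

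At stake is the reading of the main result. A significant difference could partly reflect who was left in the analysis, and a true difference could be distorted. The Discussion intends the findings to inform whether oral health promotion enters stroke care.

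This is not a detail left to an unseen analysis plan. The article itself fixes the set for the primary outcome.

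**Working it through.** **Inputs from the protocol article:** 40% (comparison) and 20% (intervention); significance level 0.05, sidedness not stated; power 80%; 10% first-week dropout; 83 per group.

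**Assumptions (not in the article):** the fraction *f* removed from the intervention arm only, and the pneumonia risk *r* of those removed.

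**1. The plan's own figure.** With a one-sided 0.05 test and continuity correction, 40% versus 20% at 80% power needs 74 per group; 74/0.9 = 82.2, so 83. This reproduces the stated number. The two-sided pooled formula gives 82, and 82/0.9 = 91.1, so 92. The sample size therefore rests on detecting a reduction, which is a superiority question.

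**2. Spurious benefit under no true effect.** If both arms have a true risk of 40%, the per-protocol intervention risk is

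p = (0.40 − f·r) / (1 − f).

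The chance of a significant result favouring the intervention, at two-sided 0.05, is

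Φ[(d − 1.96·SE₀) / SE₁],

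where d = 0.40 − p, SE₀ uses the pooled risk, SE₁ the separate risks, and the group sizes are 83 and 83(1 − f).

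| f | r | p | d (points) | Chance of a significant result favouring the intervention |
|---|---|---|---|---|
| 10% | 40% | 40.0% | 0 | 2.5% |
| 10% | 60% | 37.8% | 2.2 | 4.7% |
| 10% | 80% | 35.6% | 4.4 | 8.2% |
| 20% | 60% | 35.0% | 5.0 | 9.0% |

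Example, second row: p = (0.40 − 0.06)/0.90 = 0.378. With 83 and 74.7 patients, SE₀ = 0.0778 and SE₁ = 0.0777, so (0.0222 − 0.1525)/0.0777 = −1.68, and Φ(−1.68) = 0.047.

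The 10% is the protocol's dropout figure, but placing it all in one arm is an assumption. If both arms lose the same fraction at the same risk, p is the same in both and d = 0.

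**3. The opposite direction.** Suppose the true risks are 40% and 20%, and half of the pneumonia cases in each arm are excluded, for example through the antibiotic rule. Per 100 patients, 40 becomes 20 of 80 = 25.0%, and 20 becomes 10 of 90 = 11.1%. The absolute difference shrinks from 20 to 13.9 points.

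**4. What the all-randomised analysis costs.** If an assumed 10% of the intervention arm do not adhere and carry the control risk, the intervention rate is 0.9 × 20% + 0.1 × 40% = 22%. Two-sided power with 83 per arm is then 71%, against 81% at 20% versus 40%. For 5%, 15% and 20% non-adherence it is 76%, 66% and 60%. For comparison, a per-protocol test on about 75 per arm (10% lost from each arm) at 20% versus 40% has 77%.

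**The case against.** **The equivalence label could explain the choice.** Per-protocol analysis has a recognised place in equivalence trials. But with no margin, an aim of reduction and a sample size built on 40% versus 20%, the label conflicts with the rest of the design. It has to be reconciled and does not justify the set.

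**Per-protocol is limited to the bivariate analyses, and a regression with LOCF follows.** This is correct, and the regression may keep some patients whose outcomes are missing. It does not restore a randomised comparison: its set is unstated, it is not declared primary, and its stated purpose is confounding. Patients enter free of lower respiratory infection, so carrying the baseline state forward would count a patient lost in the first week as free of pneumonia.

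**The bias need not favour the intervention.** A reader might infer that high-risk patients drop out of the intervention arm only, so that the expected bias is towards benefit. The article does not support that:

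- Per-protocol is not defined, and no adherence threshold is given.
- The withdrawal and antibiotic rules apply to both arms.
- Primary caregivers are made responsible for the oral care, and most patients are inpatients in the first week. This weakens the link from deterioration to non-adherence.
- Step 3 shows that a true difference can shrink.

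This objection stands as to direction and size. It does not defend the per-protocol set, because a bias of unknown direction is itself a reason to keep the randomised comparison primary.

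**The illustration rests on chosen inputs.** It does. The only first-week loss that the article states is 10%, and it states no risk for those lost.

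**Conclusion.** The point holds in this form: the article assigns the per-protocol set to the primary between-group test and to the secondary bivariate comparisons of a superiority trial, and it names no all-randomised analysis. The result can be biased in either direction.

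The size cannot be derived from the article. If 10% are lost from the intervention arm only, at 60% to 80% risk and with no true effect, the spurious benefit is 2.2 to 4.4 points and the favourable error rate 4.7% to 8.2% instead of 2.5%. At 20% lost and 60% risk these are 5 points and about 9%. All of this depends on the assumed one-arm loss and the assumed risk. It vanishes under the null if losses are alike in both arms or carry average risk. A claim that the plan is expected to favour the intervention would go beyond the text.

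Because the primary comparison is affected, this should be corrected before the data are analysed.

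**What to change.** - Name all randomised patients, analysed in their assigned group, as the primary set for 1-week pneumonia and the main set for the secondary between-group comparisons.
- Collect first-week pneumonia status for every randomised patient, whatever the adherence or antibiotic use, and do not remove patients from this analysis because of antibiotic use after randomisation.
- Keep per-protocol as a labelled sensitivity analysis, with its membership defined in advance.
- State the analysis set of the regression and its standing relative to the chi-square test.
- Reconcile the equivalence label with the superiority hypothesis.

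**Cost.** For the primary outcome this is mainly wording plus complete first-week follow-up. The section on assessing pneumonia regards diagnosis as feasible in that week because most patients are in hospital. Non-adherence will dilute the effect: at an assumed 10%, two-sided power is about 71% with 83 per arm, and 103 analysed per arm would be needed for 80%. The later secondary outcomes need a missing-data method for withdrawn patients, and the article itself expects pneumonia to be hard to diagnose after discharge.

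### Continuous secondary outcomes are compared by unadjusted tests at each visit although their baseline values are collected, and two other named methods do not suit the outcomes they would reach

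*Protocol article*

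**What the plan says.** The Data management section names its tests by type of variable. For normally distributed continuous outcomes, a Student "test for independent samples will be performed to compare the mean of the outcomes between the groups at baseline and follow-up reviews". For non-normal ones, Mann-Whitney is used at the same time points. Change within a group is tested by the paired t or Wilcoxon signed-rank test, and for categorical outcomes "the McNemar test will be performed to identify the changes in prevalence over time within a group". Categorical outcomes are compared between groups by chi-square. These bivariate analyses are per-protocol.

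The same section then plans regression to deal with confounding: linear, negative binomial (for continuous variables that are over-dispersed) or logistic. It does not name the covariates, and it does not say whether the bivariate or the regression result takes precedence.

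The abstract has questionnaires and oral examinations at baseline and at 1, 3 and 6 months. The section on other confounding factors lists demographic, behavioural and functional data, ending with "cognitive ability as assessed by Mini-Mental State Examination [32], and number of comorbidities". The selection criteria also use two further scores: "having dysphagia as shown by Gugging Swallowing Screen (GUSS) test" and "Barthel Index (BI) scores of < 70".

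On the primary endpoint, the Outcomes section states: "The primary outcome is the prevalence of pneumonia complicating stroke within 1 week after baseline". Eligibility requires "having onset of stroke within 3 days and free of any post-stroke complication".

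**The concern.** A person's plaque, bleeding and quality-of-life scores usually correlate with that person's own earlier scores. A raw comparison at follow-up leaves this predictable part of the variation in the error term, and leaves any chance baseline difference in the estimate. The baseline t test that the plan also names removes neither.

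The within-group tests raise a separate risk. They do not compare the arms, so a significant change in one arm, or in both, is not evidence for the intervention. For pneumonia the problem is sharper, because the outcome cannot be present at entry.

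Finally, the negative binomial rule is worded for continuous variables. Two of the main continuous outcomes, plaque and bleeding, are percentages of sites with a ceiling at 100, and a count model has no such ceiling.

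At stake are the precision of the secondary outcomes and the way their p-values are read. The validity of the randomised comparison is not at stake.

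**Working it through.** **1. The plan's own figure.** The only sample-size calculation concerns the primary outcome: "in the comparison group, the prevalence of pneumonia complicating stroke within 1 week is 40"% against 20%, power 80%, level 0.05, dropout 10%, giving 83 per group. A one-sided calculation with continuity correction gives 74 evaluable per group, and 74/0.9 = 82.2, rounded up to 83, which matches. A two-sided pooled calculation gives 82 evaluable, and 82/0.9 = 91.1, rounded up to 92. The documents do not state sidedness. There is no planned figure for the continuous secondary outcomes, so the steps below take 74 evaluable per arm as an illustration. The 10% dropout is stated for the first week only, so fewer patients may remain at 1 to 6 months. The ratios in step 2 do not depend on this number.

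**2. Baseline adjustment of continuous outcomes.** With ρ the correlation between baseline and follow-up, the variance of the ANCOVA comparison divided by that of the raw comparison is 1 − ρ². The equivalent gain in patients is 1/(1 − ρ²). The raw difference detectable with 80% power (two-sided 0.05) at 74 per arm is (1.960 + 0.842) × √(2/74) = 0.461 SD; with adjustment it is multiplied by √(1 − ρ²). The values of ρ are assumptions.

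| ρ | Variance ratio | Variance cut | Patients, equivalent | Detectable difference | Power for an effect the raw test detects with 80% |
|---|---|---|---|---|---|
| 0 | 1.00 | 0% | ×1.00 | 0.461 SD | 80% |
| 0.3 | 0.91 | 9% | ×1.10 | 0.439 SD | 83.6% |
| 0.5 | 0.75 | 25% | ×1.33 | 0.399 SD | 89.9% |
| 0.7 | 0.51 | 49% | ×1.96 | 0.329 SD | 97.5% |

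**3. McNemar applied to pneumonia.** Patients are free of complications at entry, and the outcome is occurrence within 1 week or within 1, 3 and 6 months. Every discordant pair from baseline therefore goes from no to yes. With k cases in an arm the exact two-sided p-value is 2 × 0.5^k:
- k = 5: 0.0625
- k = 6: 0.031

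At the plan's own rates and 74 per arm, the expected numbers of cases are 0.40 × 74 = 29.6 and 0.20 × 74 = 14.8. The binomial probability of at least 6 cases is above 99.9% in the comparison arm and 99.86% in the intervention arm. The test would be significant in both arms almost surely, even if the intervention worked exactly as hoped.

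**4. Negative binomial.** The clinical oral health section defines the plaque and bleeding outcomes as the percentage of sites scoring 2 or 3 and the percentage of bleeding sites. These are proportions bounded at 0 and 100. A negative binomial model describes counts from zero upward without a ceiling.

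**The case against.** A reader might infer several stronger charges. The documents do not support them.

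- **That the plan has no baseline adjustment at all.** The same section plans regression for confounding factors, including linear and logistic models. The gap is narrower: the outcome's own baseline value is not named, and the named between-group tests are raw.
- **That the swallowing score (GUSS) and Barthel Index are excluded as covariates.** The section that omits them lists other data that are also recorded. It is not a closed covariate list, and a full analysis plan may fix the model. The two scores are unnamed, not ruled out.
- **That the primary analysis is faulty, or that adjustment would restore lost power.** Pneumonia has no baseline value to adjust for, and an unadjusted chi-square is valid under randomisation. The prognostic strength of GUSS and Barthel Index is not given, and eligibility (dysphagia present, Barthel below 70) narrows the range of both. In a simulation with 74 per arm and a two-sided test, unadjusted power was 76–77%. Adjusted logistic power was about 76%, 79%, 83% and 87% when the covariate's AUC was assumed to be 0.50, 0.63, 0.74 and 0.81. The gain thus runs from nothing to about 10 points, and the documents give no basis for choosing a value.
- **That the trial is already below its stated power.** This depends on a two-sided test, which the sample-size paragraph does not state.

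It is also fair to say that the McNemar rule is general and suits other categorical data such as mucosal or prosthesis status. The negative binomial model is not expressly assigned to site percentages and could serve DMFT or OHIP-14 sums. Nor does the plan call within-group tests evidence of effectiveness.

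What stands is that the rules as worded reach pneumonia and the site percentages without exception, and that the named comparisons of continuous outcomes leave baseline values unused.

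**Conclusion.** The concern holds in a limited form, as a matter of efficiency and of choosing tests that fit. For plaque, bleeding, SF-12, OHIP-14 and GOHAI, comparing groups without the baseline value gives up 9% to 49% of variance at assumed correlations of 0.3 to 0.7; at a correlation near zero the loss is negligible. McNemar on pneumonia is uninformative, a conclusion that needs only the entry criterion and the cumulative definition of the outcome. Negative binomial regression is unsuitable if used for site percentages. None of this biases the randomised comparison or contradicts a stated figure. No power loss or recovery should be claimed for the primary outcome.

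**What to change.** In the Data management section:

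1. Make a baseline-adjusted model the between-group analysis of the continuous secondary outcomes: either ANCOVA at each visit, or one repeated-measures model with treatment, visit, treatment-by-visit and the baseline value. State that it takes precedence over the bivariate tests.
2. For percentages of sites with plaque or bleeding, replace negative binomial by a fractional or binomial logit with robust standard errors, also adjusted for baseline. Restrict negative binomial to counts.
3. Exclude pneumonia from the McNemar rule, and state that within-group tests are descriptive and not evidence of effect.
4. Keep the chi-square for pneumonia. The logistic regression already planned could include GUSS, Barthel Index and age if the numeric scores are kept as trial data. The article shows the first two used for eligibility but does not say that the scores are retained. Present this as possible precision, with no promised gain.

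The cost is analysis wording. Items 1 to 3 need no new data, visits or patients; item 4 needs only that the screening scores be retained. The wording should be fixed before allocation is revealed.

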Next-generation sequencing (NGS) technique at the 16S rRNA level will be employed in this proposed trial to assess the change of the composition and relative abundance in the oral microbial community. NGS technique enables us to sequence a great number of genes at one time and profile taxonomic composition at the genus or species level with a deeper coverage of microbial community [20].

We proposed this randomized controlled, parallel, single-blinded, equivalence trial with an allocation ratio of 1:1, which compares the effectiveness of powered tooth brushing with adjunctive use of chlorhexidine mouth rinsing and oral health instruction (OHI) versus OHI in (1) reducing the prevalence of aspiration pneumonia complicating stroke, (2) changing the composition and relative abundance in the oral microbial community, (3) improving oral hygiene status in terms of reducing dental plaque and gingival bleeding, and (4) improving oral health-/generic health-related quality of life.

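### The primary outcome has both a per-protocol chi-square and an adjusted logistic regression, with no statement of which answers the primary question

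*Protocol article*

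**What the plan says.** The Outcomes section sets a single primary endpoint: "The primary outcome is the prevalence of pneumonia complicating stroke within 1 week after baseline". The only statement of alpha is in the sample size paragraph under Participants: "We set the statistical power at 80% and the statistical significance level at 0.05".

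The Data management section then contains two between-group analyses that reach this endpoint.

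- **Unadjusted.** "Per-protocol (PP) will be employed for both primary and secondary outcomes in bivariate analyses". For categorical outcomes the between-group test is the chi-square. This is the only analysis sentence that mentions the primary outcome by name.
- **Adjusted.** "Regression analyses will be employed to address the effect of confounding factors for outcomes". For the type of model: "Logistic regression will be adopted when the dependent variables are binary". LOCF for missing follow-up outcomes is specified for the regression only.

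The candidate adjustment factors are listed under Collection of other confounding factors. The article does not call either analysis primary, supportive or sensitivity, and it gives no order between them.

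**The concern.** The two analyses can differ in three ways: the patients they count, the treatment of missing outcomes, and the effect measure (an unadjusted difference in proportions against a covariate-adjusted odds ratio). They can therefore give different answers to the same question. If one is significant and the other is not, the article offers no rule for which is the trial's result, and the choice could be made with both p-values in view.

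The analysis that the text leans towards is also the weaker one for a deciding role. It drops patients after randomisation in a trial whose participants know their allocation. One arm has a brush and a rinse to use for 6 months, so per-protocol exclusions need not fall equally on the two arms.

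**Working it through.** **Inputs from the protocol.** Rates for the 1-week outcome: comparison group "the prevalence of pneumonia complicating stroke within 1 week is 40" per cent; for the other arm, "the prevalence could be decreased to the lower limit of 20% in the interventional group". Allocation: "with an allocation ratio of 1:1". Sample size 83 per arm, dropout 10% in the first week, alpha 0.05, power 80%. Patients enter free of post-stroke complications.

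**1. The plan's own sample size.** The pooled two-proportion formula is n = [z_α √(2p̄q̄) + z_β √(p₁q₁ + p₂q₂)]² / (p₁ − p₂)², with p̄ = 0.30.

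- Two-sided: (1.960 × 0.6481 + 0.8416 × 0.6325)² / 0.04 = 81.2, so 82 per arm; with dropout, 82/0.9 = 91.1, so 92.
- One-sided with continuity correction: 74 per arm; 74/0.9 = 82.2, so 83, the stated figure.

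Either way it is an unadjusted comparison of two proportions. Sidedness is not stated and is a separate matter.

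**2. The two analyses need not estimate the same thing.** If the 10% who drop out are a random subset and are simply omitted, the expected rates stay at 40% and 20%, a difference of 20 points. If their last observation, no pneumonia, is carried forward, the rates become 0.9 × 40% = 36% and 0.9 × 20% = 18%, a difference of 18 points. This assumes that no event was seen before dropout.

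**3. False-positive rate if either result could count.** Limits: 1 − 0.95² = 9.75% for independent tests, and 0.05 + 0.05 = 10% as the ceiling. The tests share most of their data, so the true figure is lower.

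Simulation with no treatment effect, event rate about 40%, 83 per arm, 10% missing at random and coded pneumonia-free in the regression, 6,000 trials per row. Covariate effects and extra per-protocol exclusions (here in both arms) are assumptions. Slope is the log-odds per SD of the combined covariate score.

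| Covariates | Slope | Extra exclusions | Chi-square | Logistic | Either |
|---|---|---|---|---|---|
| 5 | 0.5 | 0% | 5.63% | 5.73% | 7.30% |
| 5 | 0.5 | 10% | 5.23% | 5.27% | 7.50% |
| 11 | 0.5 | 10% | 5.05% | 6.00% | 8.30% |
| 11 | 1.0 | 10% | 5.42% | 5.95% | 8.58% |
| 11 | 1.0 | 20% | 5.05% | 5.72% | 8.58% |

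Monte Carlo standard error for the last column is about √(0.08 × 0.92/6000) = 0.35 points.

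A second set of assumptions used six covariates, three of them with log-odds 0 to 0.8 per SD. Half of the dropouts' events went unseen, and 0, 10 or 20% of the intervention arm only was excluded (2,500 trials per scenario). It gave chi-square 4.8–5.6%, logistic 5.0–5.9%, either 6.8–8.4%. With both tests run on the same per-protocol data, either-significant is about 6.4–7.9%. Overall: roughly 6–9%.

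**4. Disagreement at the design effect.** Under the second set of assumptions with 40% against 20%, exactly one of the two tests was significant in 7.0–20.5% of trials. Repeat runs gave much the same, so roughly 8–20%.

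**5. Why the covariate list must be short.** Expected events at the design rates are 83 × 0.40 + 83 × 0.20 = 49.8. The protocol lists eleven candidate factors. With one coefficient each plus the arm, that is 49.8/12 = 4.2 events per coefficient. With three factors plus the arm it is 49.8/4 = 12.5.

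**The case against.** The text does lean one way. Only the per-protocol sentence names the primary outcome, and the sample size is an unadjusted two-proportion calculation inflated for dropout, which suits an analysis that loses dropouts. The regression has a narrower stated purpose, to deal with confounding, and an unadjusted comparison followed by an adjusted one is a conventional sequence. Labelling analyses and fixing covariates are also often left to an analysis plan, which is not shown here. All of this stands, and a bare request for labels would be a request for missing detail.

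A reader might go further and infer that the trial runs two full-alpha tests on two different data sets, with an error rate above 5%. The article does not support that. The 0.05 appears once, in the sample size paragraph. No sentence says that success on either test is enough. The population for the regression is not named; that it includes patients missing from the per-protocol set is only suggested by LOCF being confined to the regression. Each test alone is sound, and some disagreement between a main and a sensitivity analysis is normal.

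What remains is that the regression sentence covers all outcomes, that a lean is not a designation, and that the analysis favoured by the lean is a per-protocol one. The Background does call this an equivalence trial, where a per-protocol analysis has a traditional place. But the sample size paragraph posits a reduction from 40% to 20%, which is a superiority question.

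**Conclusion.** The point holds in a limited form. The article gives its one primary outcome two analyses with different missing-data handling and no order between them, and the one tied to it by name is not the best choice to decide the trial. There is no demonstrated inflation of the type I error: about 5–6% for each test alone, and roughly 6–9% only under an either-result rule that the article does not state. The more practical risk is that the two conflict, in roughly 8–20% of trials if the design effect is true, with nothing in the article to settle which one stands. The event rates, arm size and 10% dropout are the protocol's. The covariate effects, the pattern of missing outcomes, the per-protocol exclusion rates and the use of all 166 patients in the regression are assumptions. This should be settled before allocation is revealed, but it does not undermine the design.

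**What to change.** State in the Data management section, or in the analysis plan with a cross-reference, that the primary question is decided at 0.05 by one between-group comparison of 1-week pneumonia in all randomised patients. Use logistic regression adjusted for a short pre-specified list of the baseline factors already collected (for example age, cognitive score and number of comorbidities), and report it with a risk difference, the scale on which the trial was sized. The same sentence should say how a missing 1-week outcome enters this analysis; at 10% dropout that concerns about 83 × 0.10 = 8 patients per arm. Label the per-protocol chi-square and the LOCF regression as sensitivity analyses that cannot replace the deciding one.

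The cost is wording. The factors are already recorded, the sample size stays at 166, and the sponsor gives up only the choice between results. Keeping both tests as deciding analyses at 0.025 each would cost more: by the unadjusted two-sided calculation, power would fall from 76.7% to 67.1% with 75 evaluable patients per arm (83 × 0.9 = 74.7), or from 80.9% to 72.0% with all 83.
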